#### Intervention description {11a}

The study will start at the same time at all participating sites that will continue to provide routine clinical care according to their current policies. Prospective data gathering will be accomplished.

A start point for the experimental intervention (3, 6, 9, or 12 months from the start of the study) will be assigned for each clinical site (1 to 5) taking into account the expected time internally needed to overcome all logistics and regulatory issues with a potential impact on FICare implementation. A 3-month wash-out period will be used for the local training process and assessment of site readiness, while enrolment will be halted. After that, recruiting will continue, and the experimental intervention will be started. Clinical sites 6 and 7 will run the experimental intervention from the start of the study, without pauses.

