## Statistical methods

### Statistical methods for primary and secondary outcomes {20a}

The primary analysis will be conducted in the intention-to-treat (ITT) population including all enrolled patient-family dyads who received at least one task training according to protocol procedures.

Descriptive statistics will be recorded for each group with mean, median and standard deviation for numerical variables and absolute and relative frequencies for categorical variables. 95% confidence intervals (CIs) will be provided. Comparisons between control and intervention groups will be performed using chi-square tests for categorical variables, analysis of variance for normally distributed continuous variables, and Mann–Whitney or Kruskal–Wallis tests for non-normally distributed continuous variables. Through a mixed-methods research approach and techniques both quantitative and qualitative, the following impacts will be evaluated: (a) effect of intervention: the control and the intervention group dataset from the non-FICare-experienced centres will be compared; (b) effect of “expertise” on outcomes: comparisons will be conducted between datasets from already trained FICare centres and those from the non-FICare-experienced centres.

Socio-economic sustainability: Health economics analysis based on the value of implementation framework will be conducted to assess the cost-effectiveness of RISEinFAMILY implementation strategies. The difference between the total net benefit of perfect adoption and the total net benefit of current implementation will generate the expected value of perfect implementation (positive values would characterise cost-effective implementation strategies). The analysis will also allow identifying differences in delivering RISEinFAMILY in different countries/health care settings.

Psychological assessment of experiences collected by either the NICUs staff and the families enrolled in the pilots will be conducted. Gender differences will be explored in relation to socioeconomic and cultural background.

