For our primary hypothesis, we will compare infant standardised weight gain velocity between the two groups over the 4-week study period using generalised linear mixed modelling (GLMM). For our primary outcome, we will compare infant standardised weight gain between the two groups over the study period defined as the change in Patel’s growth pattern measured weekly from enrolment until day 28 post-enrolment, testing an interaction term between group and post-baseline weight measurements. We will adjust for additional covariates using a hybrid approach, forcing in known confounders of gestational age and study site and using backward stepwise selection to retain covariates that contributed *p* < 0.1 to the final model from potential confounders. Additionally, we will conduct sensitivity analyses by adding in weight measured at discharge.

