### Methods for additional analyses (e.g. subgroup analyses) {20b}

Important prognostic variables are centre, sex and gestational age, or main neonatal diagnosis. These will be used as additional independent variables in key secondary logistic regression models for secondary subgroup analysis.

Further subgroup analysis will be conducted in line with the primary analysis, where the endpoint is dichotomous. For continuous endpoints, similar modelling strategies will be used, but instead of logistic regression linear regression models will be used.

The cost-effectiveness analysis of RISEinFAMILY implementation will be carried out using recommended methods [35, 36]. A decision-analytical [37] will be developed and populated with costs and effectiveness data from the pilot studies. For each RISEinFAMILY implementation site, the cost-effectiveness of the intervention will be estimated. The cost-effectiveness and the value of implementation analyses will be conducted for the seven neonatal units involved in the study. The mean net monetary benefit per participant will be calculated using the health care system willingness-to-pay threshold corresponding to the current cost of neonatal care in the NICU.

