### Methods in analysis to handle protocol non-adherence and any statistical methods to handle missing data {20c}

Incomplete data will be addressed using multiple imputation chain equations (mice), taking into account clustering adjustments. Rubin’s rules will be employed to combine the findings from various imputed datasets. Following the recommendations of the Panel on Handling Missing Data in Clinical Trials, sensitivity analyses will be conducted with diverse strategies for handling missing data, incorporating adjustments for clustering. This will encompass considering missing data scenarios such as completely at random, missing at random and missing not at random.

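### Apart from weight gain, the stated control-versus-intervention tests carry no site, cluster or calendar-time term, so a secular trend, and possibly site mix, can pass for an intervention effect

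*Protocol article*

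**What the plan says.** All references are to the Protocol article.

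- **Statistical methods {20a}**, headed for primary and secondary outcomes: "Comparisons between control and intervention groups will be performed using chi-square tests for categorical variables". Analysis of variance is named for normally distributed variables and Mann-Whitney or Kruskal-Wallis tests for the others. For the effect of the intervention, "the control and the intervention group dataset from the non-FICare-experienced centres will be compared". No site, cluster or period term is attached.
- **Same section, mixed model:** "For our primary hypothesis, we will compare infant standardised weight gain velocity between the two groups". This model adjusts by "forcing in known confounders of gestational age and study site". It is stated for the primary hypothesis and growth outcome only.
- **Additional analyses {20b}:** centre, sex and gestational age or main diagnosis are listed as prognostic variables. "These will be used as additional independent variables in key secondary logistic regression models for secondary subgroup analysis". Linear regression replaces logistic for continuous endpoints. No time term is named.
- **Missing data {20c}:** "multiple imputation chain equations (mice), taking into account clustering adjustments". Clustering is named here only for imputation and the missing-data sensitivity analyses.
- **Intervention description {11a}:** "A start point for the experimental intervention (3, 6, 9, or 12 months from the start of the study) will be assigned" to each of sites 1-5, "taking into account the expected time internally needed to overcome all logistics and regulatory issues". Enrolment then halts for three months. Sequence generation {16a} says that allocation is not randomised.
- **Discussion:** asserts that the analysis considers time. No methods section names such a term.

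**The concern.** In a stepped wedge the control data precede the intervention data at every site. A two-sample test on the pooled data cannot separate the intervention from anything else that changed over the study. It also treats infants of one unit as independent. If the ratio of control to intervention infants differs between hospitals, it mixes differences between five countries into the group comparison.

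The outcomes exposed are nosocomial infection, necrotising enterocolitis, brain injury, feeding, and parental stress, anxiety and depression, as well as primary implementation measures such as kangaroo-care time if compared between groups. The Objectives section seeks superiority on infant clinical outcomes and parental mental health, so a false benefit or harm here would bear on the trial's claims.

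**Working it through.** **The plan's own figure.** Sample size {14}: difference 1.9, SD 2.5 g/kg/d, alpha 0.05, power 95%. Normal approximation, two-sided: 2 x (1.960 + 1.645)^2 x 2.5^2 / 1.9^2 = 45.0. The t-test solution is 45.98, hence the stated 46 per group. It reproduces, as a calculation for independent infants without clustering.

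**Inputs.** From the article: starts at 3, 6, 9 or 12 months, a 3-month halt, 32 months, five sites, 552 babies over seven sites. Assumed: one schedule using all four starts (3/6/9/12/12), the halt following the start point, even enrolment, and 460 infants at sites 1-5 (5 x 92) unless stated. ICC, trend and site risks are assumed throughout because the article gives none.

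**Site mix.** A site starting at month s gives s control months and 29 - s intervention months.

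| Start | Control months | Intervention months | Share of controls | Share of intervention |
|---|---|---|---|---|
| 3 | 3 | 26 | 7% | 25% |
| 6 | 6 | 23 | 14% | 22% |
| 9 | 9 | 20 | 21% | 19% |
| 12 (two sites, each) | 12 | 17 | 29% | 17% |
| Total | 42 | 103 | 100% | 100% |

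**Calendar time.** Mean time of controls: (9 + 36 + 81 + 144 + 144) / (2 x 42) = 4.9 months. Mean time under intervention: (26 x 19 + 23 x 20.5 + 20 x 22 + 2 x 17 x 23.5) / 103 = 21.4 months. The gap is 16.5 / 32 = 0.51 of the study.

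- Risk falling linearly from 20% to 15%, no true effect: expected rates are 20 - 5 x 4.9/32 = 19.2% and 20 - 5 x 21.4/32 = 16.7%. Simulated chi-square rejection is about 10-12%. It is about 12% even with exactly 46 + 46 infants at every site.
- Continuous outcome with a 0.3 SD trend over the study: expected spurious difference 0.3 x 0.51 = 0.15 SD. Simulated t-test rejection is 32-39% at ICC 0 to 0.10, and 41-43% with 46 + 46 per site. At ICC 0.05, adjusting for site alone gives 35.4%; site plus 3-month period gives 4.8%.

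**Clustering and site mix, no trend.** The variance of the crude difference relative to what the test assumes is

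VIF = [ICC x sum(share difference)^2 + (1 - ICC) x (1/nc + 1/ni)] / (1/nc + 1/ni).

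Here nc = 133 and ni = 327, so 1/nc + 1/ni = 0.0106, and the sum of squared share differences is 0.0688.

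- ICC 0.05: VIF = (0.00344 + 0.01004) / 0.01057 = 1.28. Type I error is P(|Z| > 1.96/sqrt(1.28)) = 8.3%.
- ICC 0.10: VIF = 1.55; 11.6%. Simulation gives 12.3%, and 4.7% with site and period in the model.
- With 46 + 46 at every site the share differences are zero, and the test is slightly conservative (4.4% and 3.9%).

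**Risk gradient aligned with start order (a scenario).** Site risks 10%, 16.7%, 23.3%, 30%, 30% in start order; 552 x 145/209 = 383 infants at sites 1-5 (145 = 5 x 29 months; 209 adds 2 x 32). Crude rates are about 25% in controls and 21% under intervention. Over the four possible start patterns the chi-square test rejects in about 13-22%. Placing the same risks on the 3/6/9/12/12 schedule in every possible order gives about 7% on average (range 4-16%). A 15-25% gradient in start order gives 7-9%.

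**The case against.** The strongest reply has four parts.

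1. **Other regressions are planned.** A reader might infer that only growth gets a model. That goes too far: {20b} names logistic and linear regressions with centre. Its heading and wording tie them to subgroup analysis, however, and no time term appears, so they do not replace the main comparison.
2. **The quoted sentence follows one on descriptive statistics** and is not expressly limited to secondary outcomes. That is true. But the section lists the effect of the intervention among what will be evaluated by comparing groups, and no other main analysis is stated for these outcomes.
3. **Site mix need not differ.** A reader might infer that the staggered starts guarantee imbalance. They do not. {16a} aims at an equitable distribution between groups, and 552 = 5 x 92 + 2 x 46 is compatible with 46 + 46 at each of sites 1-5. The article neither states nor excludes that balance. With it, the site-mix bias vanishes; the calendar-time bias remains.
4. **Readiness is not risk.** A reader might take 13-22%, favouring the intervention, as the expected error. Nothing links logistic or regulatory delay to infection risk, and the direction merely repeats the assumed gradient.

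A further point, that chi-square and rank tests do not supply the estimate and standard error that Rubin's rules combine, is minor: the section also promises confidence intervals, and test statistics can be pooled in other ways.

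**Conclusion.** The concern holds for the outcomes that rest on the crude tests. This is a stated rule that does not fit the design, not detail left to an analysis plan.

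Calendar time is the firmer part, because controls come earlier at every site however enrolment falls out. The error is about 10-12% for a 5-point fall in a 20% risk, and above 30% for a 0.3 SD trend in a continuous score. Site differences add to this only if the control-to-intervention ratio varies between sites: about 8-12% at ICC 0.05-0.10 under even enrolment. The aligned-gradient figure of 13-22% is a scenario, not an estimate.

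All sizes rest on assumed trends, ICCs or risks. The ordering of control before intervention does not. The weight-gain model already forces in study site, so the site-mix part of the point does not extend to it.

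**What to change.** - Label the chi-square, analysis-of-variance and rank tests in {20a} as descriptive.
- For each secondary infant and parent outcome, and for primary implementation outcomes compared between groups, take inference from a logistic or linear (mixed) model at sites 1-5 with group, site and calendar period forced in, plus gestational age. Report an adjusted difference or odds ratio with a 95% CI.
- If site is a random effect, use a small-sample correction for five clusters.
- For rare events such as necrotising enterocolitis, specify a penalised or site-stratified version with a coarser time term, since a full set of site and period terms may be barely estimable.
- State whether enrolment is to be balanced between phases within each site.

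**Cost:** analysis wording and slightly more programming; no new data. Intervals will be wider. On the 3/6/9/12/12 schedule, control and intervention infants are enrolled concurrently only from month 6, when the first site resumes, to month 12, when the last control phase ends. The extra width reflects information that the crude tests only appear to have.

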### Outcomes {12}

The study’s primary outcomes are as follows: (a) RISEinFAMILY implementation: proportion of families completing basic and advanced training levels (observed vs expected), average time to complete basic and advanced training levels (observed vs expected) and average time of kangaroo care per day (hours); (b) short-term health infant’s outcomes: proportion of high-risk infants achieving and maintaining adequate growth patterns during NICU admission, defined according to Patel’s method [10, 11].

The study’s secondary outcomes are as follows: reported adverse event rate per 1000 patients/day, feeding patterns and major morbidities at 36 weeks postmenstrual age (PMA) or discharge, nosocomial infection [12], necrotising enterocolitis (Bell’s > stage 2), moderate-severe brain injury (worst cranial ultrasound) [13], parental needs, empowerment and psychological health (stress [14], anxiety and depression [15, 16], self-efficacy [17], bonding [18], resilience [19]), professional’s self-care and satisfaction (anxiety and depression [15], burnout [20], post-traumatic stress [21], work and well-being [20]).

The study’s exploratory outcomes are as follows: economic impact (level of post-implementation utilisation of FICare, resources and costs associated with FICare implementation, cost-effectiveness estimates compared to the current care, expected value of current implementation and expected value of perfect implementation); mid-term infant’s general health (growth pattern during the first 12 months from birth, use of health system facilities after discharge); long-term neurodevelopment (survival without neurodevelopmental disabilities).

Specific items and test batteries are stated in Additional file 1.

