### Participant timeline {13}

See Table 1.

**Table 1 Tab1:** Activity scheme

	**Screening**	**Enrolment**	**Intervention**	**End of intervention**	**Short-term endpoint assessment**	**Mid-term endpoint assessment**	**Long-term endpoint assessment**
**Date**	x	x	x	x	x		
**Informed consent document**	x						
**Signed informed consent document**		x					
**Eligibility**	x						
**Demographic and perinatal data**		x					
**Parental data**		x					
**NICU facilities**		x					
**FICare profile**		x					
**Day of life and PMA**		x		x	x	x	x
**Neonatal outcomes**					x		
**Task on training**			x	x			
**Kangaroo (hours/week)**			x				
**Weight, length, head circumference**		x	x	x	x	x	x
**Nutrition**				x	x	x	
**Maturation skills**				x	x		
**Adverse events**			x	x	x		
**Reason for early discontinuation**				x			
**General health**						x	x
**Neurodevelopment**							x
**Economic impact**^a^			x	x	x		x
**Parental questionnaires**		x			x	x	
**Staff questionnaires**^b^							

X indicates mandatory procedures that should be entered into the eCRF

*NICU* neonatal intensive care unit, *FICare* Family Integrated Care, *PMA* postmenstrual age

^a^Economic impact on newborns, carers and staff as described in Additional file 1

^b^2 measurement points: first time before FICare implementation at his/her institution; second time at least 3 months after FICare implementation at his/her institution. In FICare expert centre only one time

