## Data collection and management

### Plans for assessment and collection of outcomes {18a}

Data will be collected by researchers at participating hospitals and stored anonymously in a digital database (Research Electronic Data Capture; REDcap). Data will be stored in accordance with guidelines issued by the Spanish Data Protection Agency. Independent monitors will perform source data verification and assess the performance of trial procedures at least once a year at each site. FIBHULP will be responsible for the data management and storage of the study data. The veracity of the data will be ensured through the training of the professionals in charge of the REDCap database. In addition, a database user manual has been included in the study folder accessible to all researchers.

There will be several time points for data entry: screening, enrolment, weekly visit up to discharge to home or transfer to a non-FICare centre, short-term clinical outcome assessment, mid-term clinical outcome assessment and long-term clinical outcome assessment. If the infant in the meantime has been discharged to a step-down unit, data should be sought from the specific unit. If this is not possible, data should be used until the date of discharge to the step-down unit.

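### Staff at sites 1–5 are measured before and after implementation, but the only comparison tests stated are independent-group tests that ignore both the pairing and the site, so their standard errors are invalid

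*Protocol article*

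**What the plan says.** The Objectives section names professionals' self-care and satisfaction as one of three areas in which superiority over routine care is to be shown. Outcomes {12} lists the staff scales (anxiety and depression, burnout, post-traumatic stress, work and well-being) as secondary outcomes.

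Table 1, footnote b, in Participant timeline {13} sets the staff schedule: "2 measurement points: first time before FICare implementation at his/her institution; second time at least 3 months after FICare implementation at his/her institution". For the sites already experienced in FICare it adds: "In FICare expert centre only one time".

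The section Statistical methods for primary and secondary outcomes {20a} then fixes the tests. It begins with the categorical measures: "Comparisons between control and intervention groups will be performed using chi-square tests for categorical variables". If a continuous measure is normal, the section names "analysis of variance for normally distributed continuous variables". Where normality fails, its choice is "Mann–Whitney or Kruskal–Wallis tests for non-normally distributed continuous variables". The effect of the intervention is defined there as control data against intervention data at the sites new to FICare. A second comparison sets experienced sites against the others.

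The generalised linear mixed model later in {20a} is for infant weight gain. The regressions in {20b} are for subgroup analyses and have no person term. The clustering adjustment in {20c} belongs to the handling of missing data. None of these covers the staff comparison.

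**The concern.** At sites 1–5 a professional who follows footnote b contributes one response to the control data and one to the intervention data. Two responses from one person are normally positively correlated, and colleagues in the same unit in the same period share influences. The stated tests assume neither. Chi-square, Mann–Whitney and Kruskal–Wallis have no paired form. Analysis of variance has one, but the sentence confines it to comparing groups.

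At stake is whether the p-values and confidence intervals for the staff outcomes mean what they claim. The error can go either way. Ignoring the pairing makes the standard error too large and wastes information. Ignoring unit-level change between periods makes it too small.

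**Working it through.** **The plan's own figure.** The only sample-size calculation is for infant weight gain (Sample size {14}): difference 1.9, SD 2.5 g/kg/d, alpha 0.05 (two-sided assumed), power 0.95.

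- Normal approximation: n = 2 × [2.5 × (1.960 + 1.645) / 1.9]² = 44.996, so 45 per group.
- t-based: 45.98, so 46 per group, as stated.

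The figure reproduces, but it does not bear on staff outcomes. The article gives no staff number, effect, SD or correlation. Every staff input below is therefore an assumption, shown over a range.

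**Step 1: pairing only.** Let rho be the correlation between a person's two responses, with equal variances and everyone linked.

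- Standard error ratio, independent-group over true: 1/√(1 − rho).
- Actual size of a nominal 5% test: 2 × [1 − Φ(1.96/√(1 − rho))].
- Its power, where a paired test would have 80%: Φ(1.960 + 0.842 − 1.96/√(1 − rho)).

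| rho | SE ratio | actual alpha | power (paired test: 80%) |
|---|---|---|---|
| 0.3 | 1.20 | 0.019 | 68% |
| 0.5 | 1.41 | 0.006 | 51% |
| 0.7 | 1.83 | 0.0003 | 22% |

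**Step 2: partial linkage.** If only a share f of each wave answers both times, for example because of turnover, the ratio becomes 1/√(1 − f × rho). At f = 0.5 it is 1.085, 1.155 and 1.240 for rho 0.3, 0.5 and 0.7.

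**Step 3: add the site.** With m staff per site and a share p of the variance lying between site-periods, true variance over assumed variance is (m − 1) × p + (1 − rho). For m = 40 and rho = 0.5:

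- p = 0.01: 0.39 + 0.50 = 0.89, SE ratio 1/√0.89 = 1.06 (too large).
- p = 0.02: 0.78 + 0.50 = 1.28, SE ratio 1/√1.28 = 0.88 (too small).

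The two errors cancel when (m − 1) × p = rho, here at p = 0.5/39 = 0.013. A small site-by-period share is therefore enough to reverse the direction.

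**Step 4: does the loss of power decide the result?** At rho = 0.5 with no site-by-period variance, independent-group test against paired test:

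| pairs | effect (SD) | independent | paired |
|---|---|---|---|
| 50 | 0.3 | 26% | 56% |
| 100 | 0.3 | 59% | 85% |
| 200 | 0.3 | 93% | 99% |
| 100 | 0.5 | 99% | over 99% |

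The consequence runs from serious to negligible, depending on inputs that the article does not state.

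**The case against.** The strongest reply is that {20a} does not clearly assign these tests to staff. Section {6b} defines the control group as patients, {20a} opens with a population of infant–family dyads, and the psychological assessment of staff and families has its own sentence with no test named. On that reading the staff method is merely left to the analysis plan. This has some force, and the text is ambiguous. But the section is headed as covering secondary outcomes, the staff scales are secondary outcomes, and the sentence on tests exempts none of them. A reader who applies the article as written would use these tests.

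Analysis of variance could also be taken to include a repeated-measures form. That would rescue only the normally distributed scales, not the categorical or skewed ones, and the sentence speaks of comparing groups.

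Three stronger readings are tempting and are not supported:

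- *That the standard errors are simply too large.* Step 3 shows that they can also be too small.
- *That a true effect on burnout or well-being is likely to be missed.* Step 4 shows power above 90% in plausible cases, and none of the inputs comes from the article.
- *That a professional's two responses cannot be linked,* because {18a} says data are "stored anonymously in a digital database". Data management {19} speaks of pseudonymised data and Confidentiality {27} of a participant code. The wording in {18a} looks loose. It does not show that linkage is impossible, although no section says explicitly that the code covers staff questionnaires.

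Finally, the tests raise no pairing problem for the experienced-site comparison as far as staff there answer once.

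**Conclusion.** The point holds in a limited form. The two-occasion staff schedule at sites 1–5 does not match the independent-group tests that {20a} fixes, and no other section supplies a method that uses the pairing or the site. The resulting standard errors are invalid.

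With complete linkage and negligible site-by-period variation they are too large by a factor of about 1.2 to 1.8 (rho 0.3 to 0.7), and the test is conservative. With half the staff linked the factor falls to about 1.1 to 1.2. With enough site-by-period variation they are too small and the test is liberal. Which applies cannot be settled from the article.

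The matter concerns secondary outcomes only and leaves the infant growth analysis untouched. It should be corrected because staff outcomes belong to one of the stated superiority areas, and because pairs not linked at collection may be impossible to recover.

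**What to change.** For the before–after staff comparison at sites 1–5, replace the listed tests with a linear mixed model for scale scores, or a logistic one for cut-offs, with a random intercept per person and terms for site and calendar period. Keep staff with only one response.

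Fixed site and period terms do not in themselves carry site-by-period variation. With five sites it is hard to estimate, so the plan should either include it with a small-sample correction or name it as a limit on the inference.

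Confirm that the participant code in Confidentiality {27} also links each professional's two questionnaires, and align {18a} with the pseudonymised wording in {19}. State separately that the experienced-site comparison needs no pairing term where staff are measured once.

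The cost is analysis-plan wording and, if staff are not already coded, one code on the questionnaire. Staff already have their own consent form ({26a}). Enrolment of patients began in February 2023, so the linkage should be checked now.

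### A positive expected value of perfect implementation does not show that an implementation strategy is cost-effective, because it is only a ceiling that leaves out the uptake achieved and, as written, the cost

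*Protocol article*

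**What the plan says.** In the protocol article, Statistical methods for primary and secondary outcomes {20a}, the health economics analysis is meant "to assess the cost-effectiveness of RISEinFAMILY implementation strategies". The expected value of perfect implementation is then defined, in a sentence that begins: "The difference between the total net benefit of perfect adoption and the total net benefit of current implementation will generate the expected value of perfect". A parenthesis attached to it supplies the interpretation: "positive values would characterise cost-effective implementation strategies".

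Outcomes {12} places economic impact among the exploratory outcomes. Its components include "level of post-implementation utilisation of FICare, resources and costs associated with FICare implementation", and the value-of-implementation outputs it lists are the "expected value of current implementation and expected value of perfect implementation".

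Methods for additional analyses {20b} adds a cost-effectiveness analysis by site and says that "The mean net monetary benefit per participant will be calculated using the health care system willingness-to-pay threshold". It gives no criterion that combines a strategy's cost with the uptake it reaches.

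**The concern.** Two questions are being treated as one. The first is whether the care model is worth having and not yet fully used. The second is whether a particular way of spreading it (training staff, certifying families, supporting sites) returns more than it costs. The expected value of perfect implementation answers the first. The parenthesis in {20a} uses it to answer the second.

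The second question is the one policy makers will ask. The abstract says the value of implementation analysis can inform decisions on investing in implementation, and Objectives {7} makes sustainability, judged through cost-effectiveness, part of the project's aim. Read literally, the criterion would give the same favourable label to a strategy that pays for itself and to one that does not.

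**Working it through.** The documents state no net benefit, uptake, population size or strategy cost, so there is no published figure to reproduce. The check is algebraic, followed by an illustration with assumed numbers.

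**Notation.** N = eligible infants; b = incremental net monetary benefit per infant of the care model over current care; u0 = current uptake; u1 = uptake achieved by a strategy; C = cost of that strategy. Net benefit is taken as proportional to uptake.

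**The quantity in {20a}.**

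N × b × 1 − N × b × u0 = N × b × (1 − u0)

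- For u0 < 1 its sign is the sign of b. With N = 1,000 and b = 100 it is +100,000, +80,000 and +20,000 at u0 = 0, 0.2 and 0.8, and 0 at u0 = 1. With b = −500 and u0 = 0.2 it is −400,000.
- Neither u1 nor C appears.

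**The value of a strategy.**

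N × b × (u1 − u0) − C

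For b > 0, u1 ≤ 1 and C ≥ 0 this cannot exceed N × b × (1 − u0). A positive value of the {20a} quantity is therefore necessary for a strategy to be cost-effective, but not sufficient.

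**Illustration (assumed: N = 1,000, b = 1,000, u0 = 0.20).** The {20a} quantity is 1,000 × 1,000 × 0.80 = +800,000 in every row.

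| u1 | C | N × b × (u1 − u0) | Net value of strategy |
|---|---|---|---|
| 0.20 | 50,000 | 0 | −50,000 |
| 0.30 | 400,000 | 100,000 | −300,000 |
| 0.50 | 50,000 | 300,000 | +250,000 |
| 0.50 | 400,000 | 300,000 | −100,000 |
| 0.80 | 400,000 | 600,000 | +200,000 |
| 1.00 | 900,000 | 800,000 | −100,000 |

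Over u1 from 0.20 to 1.00 and C from 50,000 to 900,000, the net value runs from −900,000 (u1 = 0.20, C = 900,000) to +750,000 (u1 = 1.00, C = 50,000). At C = 400,000 the break-even uptake is 0.20 + 400,000 / 1,000,000 = 0.60, and the sign in {20a} cannot tell which side of it a strategy falls on.

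**Generous reading 1: net benefit at full adoption is already net of C.** With C = 400,000 the quantity is 800,000 − 400,000 = +400,000. At an achieved uptake of 50% the strategy is still worth −100,000. Cost has entered, but uptake is fixed at 100%.

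**Generous reading 2: current implementation means uptake after the strategy.** The quantity becomes N × b × (1 − u1): 500,000 at u1 = 0.50 and 200,000 at u1 = 0.80. It shrinks as the strategy succeeds and is zero at full uptake, so it cannot serve as a mark of success either.

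**The case against.** The best defence is that the parenthesis is not the whole economic plan. Methods for additional analyses {20b} promises a cost-effectiveness analysis of implementation by recommended methods, with a decision model fed with cost and effectiveness data, and names it alongside the value of implementation analysis for all seven units. Outcomes {12} lists both utilisation and "resources and costs associated with FICare implementation". The article also leaves total net benefit undefined, so cost may already be inside it. And the outcome is exploratory.

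Much of this stands. Uptake and cost are collected; it is the stated criterion that leaves them out. A reader might infer that every site with positive net benefit and incomplete uptake will be declared to have a cost-effective strategy, however costly. The documents do not support that, because {20b} plans a further analysis and nowhere says that the parenthesis overrides it. What does not stand is that {20b} cures the problem. It states no rule of its own for judging a strategy and does not amend the one in {20a}, and the net-of-cost reading still presumes complete uptake.

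A reader might also object to {20b} for valuing net benefit "using the health care system willingness-to-pay threshold corresponding to the current cost of neonatal care in the NICU", on the ground that a threshold must be money per unit of effect. The article does not name the effect unit. The wording is coherent if effect is counted in NICU days, and the unit may properly sit in the full protocol. No error is shown there.

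**Conclusion.** The interpretation attached to the expected value of perfect implementation in {20a} is wrong as written. A positive value shows that the care model has positive incremental net benefit over current care and is not fully adopted. It does not show that a strategy for spreading it is cost-effective. The algebra does not depend on the illustrative figures; it assumes only that total net benefit scales with uptake. The size of the error in this trial cannot be stated, because the documents give no inputs. In the assumed example, a constant +800,000 covers strategies worth anything from −900,000 to +750,000.

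The reach is limited. This is an exploratory economic outcome, the primary growth analysis is unaffected, and the data for a correct rule are already planned. It should still be corrected, because investment in implementation is the decision this analysis is meant to inform.

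**What to change.** In {20a}, replace the parenthesis with a rule on the strategy's own value: a strategy is cost-effective only if N × b × (u1 − u0) − C > 0. Here u1 is the observed post-implementation utilisation, u0 the uptake before the strategy, b the incremental net benefit per infant over current care, and C the implementation cost. State which costs belong to b and which to C, so that none is counted twice. Keep the expected value of perfect implementation, but describe it as the maximum worth spending on implementation. Add the net value of each strategy to the economic outputs in Outcomes {12}.

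The cost is a change of wording and one extra calculation per site. No new data are needed, since utilisation and implementation costs are already listed in Outcomes {12}.
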